## **1.0 INTRODUCTION**

### **1.1 Statement of Compliance**

The study is to be conducted in compliance with this protocol, Good Clinical Practice (GCP), the Declaration of Helsinki, Title 21 of the Code of Federal Regulations §§ 50, 56, and 812, International Conference on Harmonization E6 and ISO Standards 14155:2011 .

### **1.2 Background Information and Scientific Rationale**

The enumeration of T lymphocytes that are positive for the CD4 antigen is used to evaluate the immune status of patients with, or suspected of developing, immune deficiencies such as AIDS. The CD4 antigen is the receptor for Human Immunodeficiency Virus (HIV) and the number of CD4+ T lymphocytes declines due to programmed cell death in an HIV infection. The absolute count of CD4+ T lymphocytes (Abs CD4) and the percentage of CD4+ T lymphocytes of total lymphocytes (%CD4) are cellular parameters closely associated with HIV disease progression and patient prognosis. %CD4 measurement is particularly important in the context of infant patient management and in the context of a wide range of co-morbidities. According to World Health Organization (WHO) guidance documents regarding HIV/AIDS patient treatment, the measurement of Abs CD4 cell counts and percent of CD4+ in adolescents and adults is recommended for decision-making on initiating antiretroviral therapy (ART). Recently, the use of ART has been extended on prevention or prophylaxis.

Anemia can be induced by ART or one of the hematological abnormalities frequently observed in HIV/AIDS patients in developing countries. Anemia is usually diagnosed by measuring the concentration of hemoglobin (Hb) and by counting the number of red cells or hematocrit in whole blood. It is a common practice during the patient's routine visit, more so in pregnant women, to evaluate presence of anemia and other hematological or functional parameters to assess HIV/AIDS disease progression or control.

In the recent past, there has been an expansion of laboratory infrastructure in many developing countries. Despite this, access to CD4 testing remains a bottle neck to provision of care and treatment to HIV patients due to increased demand for CD4 tests arising from ART scale up in these regions, as well as most CD4 testing being done in few central laboratories. This often leads to delays in CD4 testing and significantly contributes to loss of patients, either who fail to return for their results or who die before initiating treatment, hence negating the gains made in the scale up of antiretroviral therapy in these areas. Attempts to overcome these huddles have lead to the development of point of care systems that can offer simple, effective and scalable means of measuring these parameters within a shorter turnaround time. This approach would allow patients to receive their CD4 and other hematological test results and possibly be put on therapy on the same day of testing.

The recent development of PIMA point-of-care (POC) CD4 test system (Alere, Waltham, MA) conducts CD4 tests within 20 minutes of sample collection using capillary blood. The test can be conducted by non-laboratory staff, and testing does not require laboratory infrastructure. However, this device provides only the absolute CD4 counts, leaving the quest for other critical parameters key in management of infant and pregnant women patients like %CD4 and Hb unattained.

The BD Point of Care CD4 System is an investigational, robust, affordable and portable CD4 and Hb system consisting of an instrument with fluorescence and light absorbance microscopy and embedded software; dried reagent cartridges with reagent quality controls; and instrument quality control. The BD Point of Care CD4 first generation will serve customers in resource limited settings of the developing

world, designed to increase access to treatment by offering accurate, timely and reliable tests that support staging and monitoring of all CD4/Hb patients, encompassing adolescents, adults as well as pregnant women and infants living in resource-limited settings of developing countries.

### **1.3 Clinical Validation and Evaluation**

The purpose of the Clinical Validation of the PEO Only/IUO BD FACSPresto™ CD4 System (including PEO/IUO BD CD4% CD4/Hb cartridge) is to plan, prepare and conduct clinical studies and present the results of the studies to support Regulatory submissions and product marketing. This study encompasses three phases: I Feasibility, II Customer Evaluation, III Regulatory Submission for CE-IVD and Regulatory Submission for FDA 510K.

KEMRI/CDC has been identified as suitable clinical study site to participate during the four phases of the PEO/IUO BD Point of Care CD4 System Clinical Validation and Evaluation. All phases of the study are briefly depicted below:

#### **I. Feasibility Phase**

This phase includes Accuracy evaluation using prototype PEO/IUO BD CD4 System and prototype PEO/IUO CD4/Hb cartridge. BD will lead the study, site staff will be involved in a supporting role. All data collected will be used by BD to complete characterization according to predefine requirements and performance evaluation of the system and cartridge.

##### **Study Summary:**

1. Prototype system will be used that includes: Instrument, embedded software, reagents, instrument QC, standards and the new BD lancet
2. Sample size: Minimum of 200 venous and 200 capillary blood specimens that provide valid results
3. BD staff will be at the site working with the proto-type PEO/IUO BD FACSPresto™ System and PEO Only/IUO CD4/Hb cartridge and KEMRI/CDC Site staff will support flow cytometry testing and Hb testing with Sysmex hematology analyzer (KX-21) .
4. Hb will be fully integrated into the study work flow
5. SSC/ERC to provide written approval to conduct protocol and informed consent and Study Agreement/Contract
6. Collect basic patient demographic information
  - a. Age, gender, co-morbid conditions (anemia, TB, malaria, other)
7. Estimated start date: July, 2013
8. Study Systems:
  - Prototype PE) Only/IUO BD FACSPresto™ System and PEO/IUO CD4/CD4% CD4/Hb Cartridge
  - CD4 predicate= FACSCalibur/Tritest
  - Hb predicate= Sysmex hematology analyzer (KX-21)

#### **II. External Customer Evaluation**

This study will be conducted after the Feasibility and before or during the Single Site Accuracy Study. Prospective single site planned for July, 2013. BD Biosciences protocol number CAS-PCMKT 1

##### **Study Summary:**

1. Single external site in Africa

2. Sample size: A minimum of 50 capillary and 50 venous blood specimens that provide valid results.
3. 2-3 week duration (assumes 14-18 venous and 14-18 capillary specimens/week).
4. Assumes study will be conducted by Principal Investigator and delegate responsibilities to 1 full time KEMRI/CDC Site staff member (testing and administrative functions).
5. EC/IRB to provide written approval to conduct protocol and informed consent.
6. Collecting basic patient demographic information.
  - a. Age, gender, co-morbid conditions (anemia, TB, malaria, other)
7. Conducted under Good Clinical Practices and GLP.
8. Under BD Oversight.
9. Estimated start date: July, 2013
10. Study Systems:
  - Production equivalent PEO/IUO BD CD4 System and PEO/IUO CD4/%CD4/Hb Cartridge
  - CD4 predicate= FACSCount/ Tritest
  - Hb predicate= HemoCue 301

### **III. Regulatory US FDA 510K Submission for market clearance**

For this phase, three activities are planned, the Accuracy, Reference interval and Stability evaluation of the PEO/IUO BD FACSPresto System and PEO/IUO cartridge. All the activities will be carried out by the KEMRI/CDC Investigator, Accuracy as multisite and Stability as two-site studies.

Accuracy prospective multisite study planned for August – October 2013, 2013. BD Bioscience protocol number CAS-PCACC1.

Stability prospective single site study planned for August - October, 2013. BD Bioscience protocol number CAS-PCAOB.

Reference Intervals prospective single site study planned for August-October, 2013. BD Bioscience protocol number CAS-PCREF.

#### **Study Summary:**

1. Clinical studies will be conducted under GCP/GCLP guidelines and data will be used for FDA 510K regulatory submission.
2. Accuracy: Multisite prospective study
  - a. Three external or more sites (3OUS)
  - b. Total cohort = A minimum of 400 specimens (400 capillary and 400 venous blood (+20%)) that provide valid results
  - c. Three external sites (1US/2OUS):
    - i. Site 1 (OUS) = 133 capillary and 133 venous blood specimens
    - ii. Site 2 (OUS) = 134 capillary and 134 venous blood specimens
    - iii. Site 3 (US) = 133 capillary and 133 venous blood specimens
  - d. Duration: 16 week assuming sites start at different time; specimen processing also assumes daily testing of 10 venous and 10 capillary specimens during five weeks processed at each study site.
  - e. Assumes 2 full time staff members (testing and administrative functions) at each site.
  - f. EC/IRB with approved informed consent and Study Agreement.

- g. BD will monitor sites and data
  - h. Estimated start date: August, 2013
  - i. Systems
    - i. PEO/IUO BD CD4 System and PEO/IUO CD4/Hb Cartridge
    - ii. CD4 predicate= FACSCalibur/ Tritest
    - iii. Hb predicate= Sysmex analyzed KX-21
3. Stability: Singlesite prospective study (1OUS)
- a. 40 capillary and 40 venous blood specimens that provide valid results
  - b. 2 number of staff members (testing and administrative functions)
  - c. IRB with approved informed consent and Study Agreement
  - d. Conducted under Good Clinical Practices and GLP
  - e. BD will monitor sites and data
  - f. Estimated start date: September, 2013
  - g. Systems
    - i. PEO/IUO BD CD4 System and PEO/IUO CD4/Hb Cartridge
    - ii. CD4 predicate= FACSCalibur/ Tritest
4. Reference Intervals: Single site prospective study (1OUS)
- a. 120 capillary and 120 venous blood specimens from hematological normal subjects that provide valid results
  - b. 2 number of staff members (testing and administrative functions)
  - c. IRB with approved informed consent and Study Agreement
  - d. Conducted under Good Clinical Practices and GLP
  - e. BD will monitor sites and data
  - f. Estimated start date: August, 2013
  - g. Systems
    - i. PEO/IUO BD CD4 System and PEO/IUO CD4/Hb Cartridge
  - h.

## 1.4 Proposed Intended Use

The BD Point of Care CD4 is an automated system for *in vitro* diagnostic use in performing the direct enumeration of CD4 absolute count, CD4 percentage of lymphocytes, and Hb concentration in human whole blood.

## 2.0 OBJECTIVES AND DESIGN

### 2.1 Primary Objective(s)

- The objective in phase I (Performance Evaluation procedure) is to -determine the method bias between the “For Performance Evaluation Only” (PEO)/ “Investigational Use Only” (IUO) labeled BD FACSPresto System versus the predicate system (IVD Tritest™ CD3/CD4/CD45 reagent with Trucount™ tubes and BD Multiset™ software on the FACSCalibur™ flow cytometer) in the determination of Abs CD4 and %CD4, using venous blood in de-identified specimens.
- The objective in phase II will be to determine the method bias between the PEO/IUO BD PFACSPresto System and PEO/IUO BD Point of Care CD4/Hb Cartridge versus the IVD

FACSCCount system (BD FACSCCount System with FACSCCount CD4 Reagents and software), FACSCalibur™ flow cytometer and HemoCue 301 in the determination of Absolute CD4, %CD4 and Hb using de-identified patient specimens.

- Three objectives are planned to cover phase III:
  1. The first objective covering accuracy is to determine the method bias between the PEO/IUO BD Point of Care CD4 System and PEO/IUO BD Point of Care CD4/Hb Cartridge versus the IVD FACSCCount system (BD FACSCCount System with FACSCCount CD4 Reagents and software) and Sysmex in the determination of Abs CD4, %CD4 and Hb using de-identified patient specimens.
  2. The second objective covering stability is to generate product claim data for stability of whole blood specimens and stained samples using the investigational system (PEO/IUO BD FACSPresto System and BD CD4/%CD4/Hb cartridge) in prospectively collected venous and capillary blood patient specimens at single external study sites.
  3. The third objective covering reference interval is to generate product claim data for normal reference intervals from normal whole blood specimens and stained samples using the investigational system (PEO/IUO BD FACSPresto System and BD CD4/%CD4/Hb cartridge) in prospectively collected venous and capillary blood from hematological normal subjects at single site.

## 2.2 Secondary Objective(s)

1. The secondary objective of this study, enshrined within phase III are the following:  
Determine method bias between the PEO/IUO labeled BD FACSPresto System versus the predicate system in the determination of Abs CD4 and %CD4, using capillary blood in de-identified specimens at three or more external study sites.
2. Determine the method bias between the PEO/IUO BD FACSPresto System versus the predicate system for Hb, Sysmex (KX-21) hematology analyzer, in the determination of Hb concentration using venous blood and capillary blood in de-identified specimens.
3. Evaluate the customer's ease of use of the IUO PEO/IUO BD FACSPresto System following brief training.

## 2.3 Overall Study Design / Outcome Measures

The design applies to Phase III, Regulatory CE-IVD and US FDA 510K Submission for market clearance (BD Protocol number: CAS-PCACC1, Version 2.0).

This is a prospective, multisite study to determine the relative bias between the PEO/IUO BD FACSPresto System versus the IVD FACSCalibur™ with BD Tritest™ CD3/CD4/CD45 and Hb Sysmex methods in their determination of Abs CD4, %CD4 and Hb concentration. The design and proposed analysis of this evaluation are based on the CLSI EP9-A2 guideline on method comparison and bias estimation using patient samples.

This study is planned to include three or more sites, three of which are external to BD that will enroll prospectively procured peripheral venous blood and capillary blood specimens from subjects willing to provide written informed consent and attending for routine flow cytometry lymphocyte subset evaluation (i.e., CD4 counting) and de-identified from the subject's health personal information. The fourth site, the

BD MedLab will enroll only prospectively procured HIV de-identified venous blood specimens from HIV infected subjects for Hb determination.

The target number for enrolled specimens providing valid testing results (i.e. meeting protocol requirements) is a minimum total of 400 specimens from children s (0-12 yrs) and adolescent/adult subjects aged  $\geq 13$  years. Specimens must also fulfill age and CD4 andHb binning requirements as described in Section 4.2.2.

## 2.4 Expected Study Duration

- I. **Feasibility Phase:** The expected study duration from start of enrollment to the completion of feasibility study testing is anticipated to span approximately three weeks.
- II. **External Customer Evaluation:** The expected study duration of the Customer Evaluation from start of enrollment to the completion of study testing is anticipated to last approximately three weeks.
- III. **Regulatory for CE-IVD and US FDA 510K Submission for market clearance:** The three activities in this phase (Accuracy, Reference interval and Stability evaluations) are expected to overlap within study duration of 16 weeks from the enrollment to completion of testing of specimen.

### Proposed Timeline

[figure not shown]

## 2.5 Study Device(s)

### 2.5.1 Investigational Device(s)

The investigational device for this study is the PEO/IUO labeled BD FACSPresto System, that consist of the instrument with integrated software (BD FACSPresto Instrument) and PEO/IUO BD CD4,%CD4/Hb cartridges with intergrated quality controls that will provide the absolute count of CD4+ T lymphocyte cells/mL of blood (Abs CD4), the percentage of CD4-positive T lymphocytes of total lymphocytes (%CD4) and concentration of Hb.

### 2.5.2 Predicate Devices

The predicate devices to be used in this Performance Evaluation procedure will involve currently marketed devices used for CD4Abs counts, %CD4, and Hb concentration measurements.

- For CD4Abs and %CD4 measurements, the BD FACSCalibur flow cytometer, BD Multiset software version 1.1 or later and BD Tritest™ CD3/CD4/CD45 reagent with Trucount™ tubes will be used to test peripheral whole blood specimens (WB).
- The predicate device to measure hemoglobin concentration is the Sysmex hematology analyzer (KX-21).

## 3.0 STUDY POPULATION

### 3.1 Description of Study Site

Since 1979 Kenya Medical Research Institute (KEMRI) has collaborated with the Centers for Disease Control and Prevention (CDC) to operate a field research station in western Kenya, near the city of Kisumu in Nyanza Province. The KEMRI/CDC Research and Public Health Collaboration was originally established as a malaria research program and has since expanded, experiencing rapid growth in terms of the number and scope of research and program activities, as well as human resources and physical infrastructure. Today, the primary research activities include malaria, HIV, TB, schistosomiasis, and emerging infections. The KEMRI/CDC Research and Public Health Collaboration is housed in three state-of-the-art facilities. Administrative offices and laboratories are located at the main KEMRI/CDC field research station at Kisian (15 minutes from Kisumu). There are currently two Clinical Research Centers (CRCs) associated with KEMRI/CDC. One CRC is located on the grounds of the **Jaramogi Oginga Odinga Teaching & Referral Hospital (JOOTRH)** formerly New Nyanza Provincial Hospital) for processing - PGH) in downtown Kisumu; which has high influx of patients, approximately 21,000 patients on care and 10,000 on treatment for HIV/AIDS. Additionally, KEMRI/CDC HIV-Research laboratory is located less than three kilometers from two other major health facilities namely, Kisumu District hospital which has about 5000 patients on care and about 5000 on treatment and Lumumba health center which has about 9000 patients on care and about 7000 on treatment. The laboratory has and is still supporting clinical trials like HPTN-052.

The laboratory has also developed population-based biochemistry, immunological and hematological reference values for adolescents and adults in western Kenya that have been utilized by recent clinical studies in this region.

### 3.2 Specimen Requirements

This study will be conducted at three or more reference laboratories specializing in flow cytometric immunophenotyping (See Appendix 1: Study sites). The study requires testing of prospectively procured

venous blood and capillary blood specimens from HIV/AIDS patients **for phase I, II and III (objective 1&2) and any persons/patients** willing to participate in the study and provide written informed consent **irrespective of their HIV status for phase III (objective 3).**

### 3.3 Inclusion Criteria

The following criteria must be met for the subject and whole blood specimens to be enrolled into this study:

Subject:

- **Phase I, II and Phase III objective 1&2:** Has been infected with HIV and willing to provide written informed consent to draw venous and capillary blood.
- **Phase III objective 3: Any persons irrespective of their HIV status who are willing to provide written informed consent to draw venous and capillary blood.**
- If minor, parent(s) are willing to provide informed consent and if child aged  $\geq 13$  yrs and above, willing to provide assent (in addition to parental/guardian consent) to draw blood.
- Agrees to grant access to her/his CD4 testing medical records **if available** for pre-screening.
- Agrees to disclose age and gender
- Agrees to disclose **any** co-morbid conditions information: malaria, tuberculosis, anemia, sickle cell anemia, infectious diseases, thalassemia and other current medical condition
- Agrees to disclose current medications.

Specimen:

- Patient has provided written informed consent for specimen draw
- Venous blood collected in a blood collection tube with EDTA anticoagulant and stored at room temperature (20-25°C) and according to the collection tube manufacturer's guidelines until enrollment.
- Venous blood drawn within an adequate time to perform post-enrollment staining within 24 hours.
- Venous blood of acceptable quality for flow cytometry testing (e.g., no hemolysis or clots and acceptable pre-analytical handling).
- Venous blood of sufficient volume:  $> 1\text{mL}$  for Sample Preparation.
- Capillary blood meets requirements for specimen donation as required.

Capillary blood applied onto the PEO/IUO BD CD4/%CD4/Hb cartridge. 3.4 Exclusion Criteria

ANY of the following is regarded as a criterion for excluding a specimen from the study:

- Unwillingness to provide written informed consent.
- Unwillingness to disclose medical information regarding previous CD4 testing results.
- Unwillingness to disclose medical information regarding co-morbid conditions.
- Enrolled specimens may be subsequently excluded from the study if found to be unsuitable for testing; for example, if visual inspection prior to acquisition shows clotting or hemolysis.

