### 13.2 Informed Consent

#### *Venous and Capillary Blood Specimens*

The site will collect specimens prospectively from HIV infected subjects (**Phase I, II & phase III objective 1& 2**) and **HIV negative subjects (Phase III objective 3)** under EC/IRB approved informed consent. The principal investigator will prepare and submit the informed consent for EC/IRB review and also translate all the consent documents into the local language and verify the accuracy of the translation by performing independent back-translation. The EC/IRB may require that additional information be included in the consent form(s). The site will provide a copy of the EC/IRB documentation (i.e. approval letter) to BD.

Written informed consent must be obtained before the donor participates in the study. The clinical site is responsible for obtaining consent in accordance with the country regulations, state, local laws and internal or facility procedures (SOPs). A thorough explanation of study procedures and implications of study participation (risks/benefits) will be provided. If the potential participant is younger than 18 years of age and not a mature minor (see below), the study details will be explained to at least one parent/guardian for parental permission and then to the minor for assent. Mature minors are defined in the Kenya National VCT guidelines as persons under 18 years of age who are pregnant, married, or a parent, and who are able to consent for themselves. However, mature minors will be strongly advised to speak with and involve their parents/guardians in the study participation process if they feel it is safe to do so. Consent may be withdrawn at any time by the donor/participant. BD can withdraw donors enrolled in the study at any time.

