**Subject:**

1. Has been infected with HIV for phase I, II and III (objective 1&2) and persons for phase III (objective 3) and willing to provide written informed consent/assent and if minor/child, parent(s)/legal guardian are willing to provide informed consent to draw venous and capillary blood from the child ?. yes/no
2. Allows access to her medical records and agrees to disclose age and gender ? yes/no (if yes \_\_\_\_ date of birth? \_\_\_\_ Gender? \_\_\_\_)
3. Agrees to disclose co-morbid conditions information: malaria, tuberculosis, anemia, sickle cell anemia, infection diseases, thalassemia and other current medical conditions ? yes/no

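### Eligibility for the reference-interval study (Phase III objective 3) admits anyone irrespective of HIV status, contradicting its objective of a normal reference interval

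*Protocol*

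**What the plan says.** The Protocol describes the objective 3 population in two incompatible ways.

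**Restrictive descriptions**
- Section 2.1, Phase III objective 3, aims to "generate product claim data for normal reference intervals from normal whole blood specimens and stained samples", using "prospectively collected venous and capillary blood from hematological normal subjects at single site".
- Section 1.3, Phase III Study Summary, item 4, sets the sample as "120 capillary and 120 venous blood specimens from hematological normal subjects that provide valid results".
- Section 13.2 names the group as "HIV negative subjects (Phase III objective 3").

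**Open descriptions**
- Section 3.3 (Inclusion Criteria) admits "Any persons irrespective of their HIV status who are willing to provide written informed consent".
- Section 3.2 opens the study to volunteers "irrespective of their HIV status for phase III (objective 3").
- Appendix 2, subject item 1, asks for HIV infection in the other parts of the study "and persons for phase III (objective 3) and willing to provide written informed consent/assent".

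Under section 3.3, malaria, tuberculosis, anemia, sickle cell disease, thalassemia and current medication are matters to disclose. The exclusion list removes people who refuse to disclose co-morbid conditions, not people who have them. The Appendix 7 donor questionnaire asks about general health, recent illness and medication, with no exclusion rule attached.

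**The concern.** A normal reference interval describes values in people free of the conditions the test is meant to detect. HIV infection lowers CD4 and anemia is low Hb, so affected participants tend to fall in the lower tail, where the lower limit is estimated. The inclusion criteria and screening form are what site staff apply, and those are the open ones.

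At stake is a product claim for Abs CD4, %CD4 and Hb. If its lower limits were too low, some reduced CD4 or Hb values would be reported as normal.

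Enrolment of infected people is plausible in this setting. Section 4.1.1 approaches HIV/AIDS patients attending for CD4 testing, section 3.5 uses convenience sampling, section 3.1 describes large HIV care populations nearby, and no separate recruitment route for objective 3 is given.

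**Working it through.** **1. Can the texts be reconciled as they stand?**

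| Place | Who may enter objective 3 |
|---|---|
| 1.3 and 2.1 | Hematologically normal subjects |
| 13.2 | HIV-negative subjects |
| 3.2 and 3.3 | Any consenting person, any HIV status |
| Appendix 2 | Any person; no item on HIV-negative or normal status |

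HIV-negative only and any HIV status cannot both be the rule. Hematologically normal is not defined anywhere in the document. Appendix 2 instructs staff to assign a study number once every item is answered yes, so an infected or anemic volunteer passes. Section 7.3 has no rule for leaving non-normal subjects out of a reference interval.

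**2. The stated sample size.** The protocol gives no coverage, confidence level or estimator for the 120, so it cannot be reproduced from stated inputs. Assume a nonparametric central 95% interval with a 90% confidence interval on each limit. The smallest n then satisfies 0.975^n ≤ 0.05. Since 0.975^119 = 0.0492, n = 119, which is consistent with 120.

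**3. Which observation is the lower limit?** Under the same assumption the rank is 0.025 × (120 + 1) = 3.03, essentially the third-lowest value.

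**4. Illustrative effect on CD4.** These inputs are assumptions, not from the protocol:
- normal CD4 lognormal, median 850 and 2.5th percentile 400, so log-SD = (ln 850 − ln 400)/1.96 = 0.385;
- infected CD4 lognormal, median 350, log-SD 0.6.

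The share of infected participants below 400 is Φ[(ln 400 − ln 350)/0.6] = Φ(0.22) = 0.59, so 41% lie above it. The expected number of the 120 below 400 is 0.025 × (120 − k) + 0.59 × k for k infected. The last column is the simulated median of the third-lowest value.

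| Infected, k | Expected number below 400 | Median lower limit (cells/µL) |
|---|---|---|
| 0 | 3.0 | about 392 |
| 3 | 2.93 + 1.77 = 4.7 | about 346 |
| 6 | 2.85 + 3.54 = 6.4 | about 291 |
| 12 | 2.70 + 7.08 = 9.8 | about 218 |

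With none infected, the limit's 5–95% sampling range is 329–454. The value for three infected lies inside that range; those for six and twelve lie below it.

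**5. Sensitivity.** With an infected median of 500 and log-SD 0.5, the limit is about 351 at 5% contamination and 314 at 10% (on average 6 and 12 of 120). With an infected median of 550 it falls from 391 to 352, 316 and 284 at 5, 10 and 15%. A parametric lognormal limit, under the step 4 assumptions, falls from 401 to 344, 300 and 266. The direction is the same throughout; the size is not.

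**6. Hb, also illustrative.** Assume normal Hb with mean 14 and SD 1.1 g/dL, and anemic participants with mean 9.5 and SD 1.2. The median lower limit falls from about 11.8 g/dL to 10.5, 9.3 and 8.6 with three, six and twelve anemic participants.

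**The case against.** The strongest reply is that the protocol does define the reference sample. Sections 1.3 and 2.1 say hematologically normal, and section 13.2 says HIV negative. The section 3.3 criteria can be read as necessary rather than sufficient, with the objective still deciding which specimens count toward the 120. Section 1.3 also gives the reference-interval study its own sponsor protocol number (CAS-PCREF); that document is not available here and may define the normal subject. This stands to the extent that bias is a conditional consequence, not an established one. It does not remove the contradiction: an objective is not a screening criterion, and this document sets its own eligibility for objective 3.

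A reader might infer from the rank of 3 that any three infected participants would set the lower limit. That does not follow. Under the step 4 assumptions, with exactly three infected, one of them supplies the third-lowest value in only about a quarter of runs; with six it is about 64%. An infected person with a normal CD4 count does not lower the limit.

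A reader might also suppose that HIV-negative status is already on file for volunteers, so that nothing new is needed. The protocol does not support this: section 3.3 asks only for access to CD4 testing records, where available.

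**Conclusion.** The contradiction is certain and lies in operative text: sections 3.2 and 3.3 and Appendix 2 admit people whom sections 1.3, 2.1 and 13.2 rule out, and no exclusion criterion, screening item or analysis rule shown removes them.

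The consequence is conditional. If sites enrol by the eligibility text and those participants are analysed, the lower limits for CD4 and Hb shift downward. The size depends on the number enrolled, their values and the estimator, none of which the protocol gives. Under the main assumptions the median lower CD4 limit drops by about 46 cells/µL with three infected (392 − 346), 101 with six (392 − 291) and 174 with twelve (392 − 218); with higher CD4 counts in the infected the drop is clearly smaller. These figures illustrate the mechanism and do not predict the result.

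The problem is confined to the reference-interval component. The primary endpoint of the accuracy study, method bias against the predicate, is unaffected.

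**What to change.** Amend the Protocol so that one population governs objective 3:

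- Align sections 3.2 and 3.3 and Appendix 2 with sections 1.3, 2.1 and 13.2, so that only HIV-negative, hematologically normal subjects count toward the 120.
- Define hematologically normal explicitly, using items already collected: disclosed conditions, current medications and the Appendix 7 questionnaire.
- Add a field for HIV status to the Appendix 2 form for objective 3.
- State that anyone who does not meet the definition is left out of the reference-interval calculation.

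The cost is a protocol and form amendment and somewhat slower recruitment of the 120. People without documented HIV-negative status could not be counted, and the protocol gives no basis for estimating how many volunteers that would affect.
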